# Effect of Zhan Zhuang Qigong on upper limb static tremor and aerobic exercise capacity in patients with mild-to-moderate Parkinson’s disease: study protocol for a randomised controlled trial

**DOI:** 10.1136/bmjopen-2021-059625

**Published:** 2022-07-11

**Keywords:** Parkinson-s disease, GERIATRIC MEDICINE, Rehabilitation medicine, Clinical trials

## Abstract

**Introduction:**

Currently, the first choice for the clinical treatment of static tremor in Parkinson’s disease (PD) is drug therapy, however side effects are common. In recent years, the effects of physical therapy on PD has become a serious research focus. Studies have indicated that aerobic and resistance exercises alleviate PD movement disorders and improve aerobic capacity, but the effects of Qigong on PD static tremor and aerobic capacity remain unknown.

**Methods and analysis:**

**Objective:**

To observe the effects of Zhan Zhuang Qigong on upper limb static tremor and aerobic capacity in patients with PD, we established a rigorous randomised, parallel-controlled, assignment hidden, evaluator-blinded protocol.

**Methods:**

Seventy-two patients with PD, at the Affiliated Hospital of Shandong University of Traditional Chinese Medicine, were recruited and randomly divided into a control (n=36) and experimental group (n=36). The intervention group received conventional medicine plus Zhan Zhuang Qigong exercises five times a week at 30 min each time, over an 8-week period. The long-term effects of Zhan Zhuang Qigong on PD was investigated after the intervention. Phyphox APP, CRST, CPET, UPDRS(II, III) were used to evaluate tremor, aerobic capacity, and motor function in groups.

**Discussion:**

We are investigating the effects of Zhan Zhuang Qigong on upper limb static tremor and aerobic capacity in patients with PD. If positive are identified, they will add a new research direction and evidence for the clinical exploration of exercise therapy for PD.

**Ethics and dissemination:**

This study was approved by the Ethics Committee of Shandong University of Traditional Chinese Medicine (Approval Number: 2021–025-KY). The Committee will be informed of any changes to the trial protocol, such as intervention intensity, outcome indicators and data collection. Study results will be presented as a paper at an international conference or in a journal.

**Trial registration number:**

ChiCTR2100053529.

Strengths and limitations of this studyCurrently, the clinical effects of physical therapy toward Parkinson’s tremor are not ideal, with no clinical studies conducted on the effects of Qigong on Parkinson’s tremor.The mobile phone tremor test and cardiopulmonary exercise test used in our outcome assessments were clinically verified as accurate and reliable.Our rigorous hidden allocation, randomised parallel controlled trial design is more reliable and accurate than pre-trial and post-trial controls previously used in Parkinson’s disease clinical trials.Staff turnover during the study intervention period may lead to bias in the final results.We are unable to investigate other forms of Parkinson’s tremor other than static tremor.

## Introduction

Parkinson’s disease (PD) is a degenerative disease of the central nervous system common in middle-aged and elderly individual.^1^ The PD prevalence in individuals aged 65–69 is approximately 0.5%–1%, and in individuals aged over 80 is 1%–3%. With increased population ageing, it is anticipated that PD prevalence and incidence will increase by more than 30% by 2030, and place tremendous pressure on families and society.^2^

As one of the main motor symptoms of PD, static tremor is characterised by rhythmic and clay ball-like tremor and is accompanied by a large amplitude and frequency of 4–6 Hz, which occurs more when the weight of affected limbs or other body structures is supported. The tremor is aggravated when general exercises (such as walking) or pressures increases, but is alleviated or disappears when the body moves at will. The tremor gradually spreads from the distal end of one limb to the other.^3 4^ Parkinson’s tremor is one of the most troubling symptoms in patients with PD, which not only reduces daily living activities, but also imbues a sense of inferiority, depression and reduces participation in society.^5^ Currently, the most effective clinical treatment for PD remains drug therapy.^2 6 7^ Levodopa is considered the best treatment compound for supplementing exogenous dopamine and controlling PD, but its long-term use gradually reduces its efficacy and leads to central and peripheral adverse reactions.^8–10^ Moreover, levodopa elicits poor responses to PD static tremor and has no effect on non-motor symptoms.^11^ Invasive surgical treatments, such as focused thalamotomy and deep brain stimulation provide significant tremor relief in the short term, but do not prevent neurodegenerative progression in underlying PD.^8 12–14^ Additionally, surgery is risky and may be accompanied by complications.^12^

In recent years, PD symptom improvement by exercise therapy has gained considerable research traction. Several studies reported that aerobic and resistance exercises alleviated PD motor symptoms, including tremor.^15–19^ Among traditional Chinese Qigong therapies, Tai Chi, Wuqinxi and Baduanjin are believed to enhance balance in patients with PD and correct abnormal gait. However, few studies have focused on PD tremor and aerobic capacity.^20^

Zhan Zhuang Qigong is a basic technique in Tai Chi, and is a static, moderate and low intensity aerobic exercise combining body and mind.^21 22^ Several clinical studies have reported the benefits of Tai Chi for PD motor and non-motor functions,^23^ Tai Chi is a low cost exercise. It reduces falls, improves posture control, improves walking ability, improves depression and insomnia symptoms and improves quality of life. As a basic Tai Chi skill, the Zhan Zhuang has many Tai Chi characteristics.^24^ For example, Zhan Zhuang movements combine body and mind, they control limb and trunk stability and change the centre of gravity with the mind. Additionally, like Tai Chi, Zhan Zhuang is also a closed circular motion technique which maintains action continuity and accuracy via adjustment, feedback, re-adjustment and re-feedback, which improve the body’s recognition of stimuli and improves involuntary tremor.^25 26^

### Methods and analysis

The study is a two-arm, randomised, parallel-controlled trial with assignment-hiding and evaluator blindness. The main objective is to investigate the effects of Zhan Zhuang on upper limb static tremor and aerobic capacity in patients with mild-to-moderate PD, so as to provide a safe, effective, low-cost and easy-to-master aerobic exercise therapy for patients with PD.

### Patient and public involvement

The public is not involved in the study design. However, we will adjust intervention intensity and other details based on how participants respond to the intervention.

### Study design and setting

The study will be conducted in the Affiliated Hospital of Shandong University of Traditional Chinese Medicine. We will include 72 patients with PD with obvious upper limb static tremor. Recruitment will begin on 1 June 2022 and run until 1 June 2023. Using the random number table method, 72 patients will be randomly divided into an intervention and control group in a 1:1 ratio. Basic patient information, including gender, age, disease course, education level, residence status and drug-use will be collected. Tremor and motor function tests will be performed at least 8 hours after patients stop taking medication.

The control group will be treated with conventional medicine and routine aerobics. According to the Chinese Guidelines for the Treatment of PD (fourth edition), walking will be selected as the aerobic exercise mode in this group,^27^ five times a week at 30 min each time for 8 weeks. A combined cardiopulmonary exercise test (CPET) (treadmill test) will be used to measure peak oxygen uptake (peakVO_2_) in patients with PD at baseline and after intervention, and also anaerobic threshold (AT) and maximum heart rate (HRmax). During training, patients exercise intensity will be controlled at moderate exercise intensity (HRmax (60%–80%) measured by CPET or 11–13 Rating of Perceived Exertion (RPE). Changes in peakVO_2_ and AT at baseline and after intervention will be evaluated for improvements in aerobic exercise capacity. Walking will be performed about 1 hour after patients take their medication, and the tremor symptoms were resolved or disappeared.

The intervention group will take conventional medicine combined with Zhan Zhuang Qigong. An experienced Qigong master will guide Zhan Zhuang exercise. Week 1 will comprise the learning phase, while weeks 2–8 will be the practice phases, to be performed five times a week at 30 min each time. Intensity HRmax (60%–80%) will be measured using a cardiopulmonary combined exercise test or RPE test grade 11–13. Patients will be issued a training instruction manual and a personal exercise calendar to record the number of weekly exercises and time of each exercise. Zhan Zhuang training will be about 1 hour after patients take their medication, and tremor symptoms were relieved or disappeared. One auxiliary staff member will oversee safety measures.

### The main points of Qigong movement of Zhan Zhuang

Individuals should stand naturally, with feet about 30 cm apart and parallel to the front; arms around, with naturally open hands and two fingertips about 15 cm apart; flex the knee hip about 5°–10° and tilt the hip forward (figures 1 and 2).

**Figure 1 F1:**
[figure not shown]
Demonstration of Qigong movement of Zhan Zhuang.

**Figure 2 F2:**
[figure not shown]
Demonstration of Qigong movement of Zhan Zhuang.

### Participants and recruitment

Using the Affiliated Hospital of Shandong University of Traditional Chinese Medicine as the base, we will visit and recruit patients from the rehabilitation and neurology departments, and post recruitment advertisements on WeChat.

We will assess upper limb static tremor according to the Unified Parkinson’s Disease Rating Scale (UPDRS) Part III and the Hoehn-Yahr classification (stages 1–3) (see figure 3).

**Figure 3 F3:**
[figure not shown]
Test flow chart. CPET, cardiopulmonary exercise test; CRST, Clinical Tremor Rating Scale; UPDRS, Unified Parkinson’s Disease Rating Scale.

### Inclusion criteria

Primary PD agrees with recommended Chinese Clinical Diagnostic Criteria for PD (2016).50–70 years old.Improved Hoehn-Yahr stage 1–3.Stable condition, taking Madopar and standing for the ‘prescribed period’.No serious cognitive dysfunction, has the ability to learn Zhan Zhuang movements; (Mini-Mental State Examination score, illiteracy >17, primary school >20 and middle school >22).Agrees to participate, and sign an informed consent sheet.

### Exclusion criteria

Secondary Parkinson’s syndrome and Parkinson’s superposition syndrome caused by cerebrovascular disease, drugs and other causes.Patients with serious heart, lung, liver, kidney dysfunction or cancer.Those individuals who cannot stand due to serious knee diseases, for example, severe knee osteoarthritis and knee trauma.Patients with dementia or serious mental illness.Patients unable to stand or walk independently due to fracture, surgery or other reasons.No tremors.The ‘opening period’ tremor is obvious after taking medication.

### Termination/shedding criteria

Patients not cooperating with prescribed exercises or exercising poor compliance.Patients whose condition deteriorates or complications arise during the study should not continue.

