### Sample size

This study is designed as a randomised controlled trial. The main outcome is the mean relief of upper limb static tremor after treatment. A review of previous studies showed that aerobic exercise could reduce upper limb static tremor amplitude by approximately 60%. It is estimated that the average tremor amplitude of the control group is approximately 76±136 mm, and the intervention group is expected to be reduced by 50 mm after training. The test level α is set at 0.05 (bilateral), the degree of certainty 1-β is set at 0.80 and the control:intervention group ratio=1:1. A sample size of 63 was calculated using *http://powerandsamplesize.com*. However, considering an abscission rate of about 15%, 72 patients with PD will be included.

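### The termination criteria do not separate stopping the exercise from leaving the study, so week 9 and week 17 outcomes can be lost selectively

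*Protocol article*

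**What the plan says.** The section Termination/shedding criteria has two entries. The first is "Patients not cooperating with prescribed exercises or exercising poor compliance". The second is "Patients whose condition deteriorates or complications arise during the study should not continue". Neither gives a compliance threshold, and neither says what ends: the training, the assessments or both.

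Four other places bear on how these entries would work in practice:

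- **Study design and setting.** Zhan Zhuang patients receive a manual and "a personal exercise calendar to record the number of weekly exercises and time of each exercise". The paragraph on the walking group controls exercise intensity but mentions no such record.
- **Randomisation and allocation concealment and blinding.** Training personnel and participants know the allocation; testers and analysts do not.
- **Adverse events.** Follow-up after withdrawal is described for a patient who leaves because of an adverse event, and it concerns that event. Outcome measurement is not mentioned.
- **Sample size and Statistical analysis.** The total is raised from 63 to 72, "considering an abscission rate of about 15"%. Outcomes are due at week 9 and week 17 (Table 1) and are compared by two-group t-tests or rank tests.

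**The concern.** Both criteria arise after randomisation. Deterioration overlaps with what the trial measures (tremor, aerobic capacity, UPDRS). Compliance can depend on which exercise was assigned and on how the patient is doing. If meeting a criterion also ends the visits, the patients without week 9 and week 17 data are not a random subset, and the arms that remain are no longer the arms that were randomised.

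Loss that is alike in both arms largely cancels in the mean difference. Unlike loss does not. Three features leave room for unlike loss: compliance is judged without a threshold, the staff who see it know the allocation, and the written adherence record is described for one arm only.

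This is more than a detail left to an analysis plan. Such a plan can define an as-randomised population, but it cannot recover a tremor recording or exercise test that was never made. Whether these patients are still measured is settled by trial conduct, and the criteria govern that conduct.

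**Working it through.** **Inputs from the Sample size section.** Control amplitude: "average tremor amplitude of the control group is approximately 76±136 mm". Planned effect: "the intervention group is expected to be reduced by 50 mm after training". Loss allowance: 15%. The document gives no loss rate by arm and no relation between loss and outcome, so those are assumed below.

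**The plan's own loss step.** 63 × 1.15 = 72.45, which matches the stated 72. Dividing instead gives 63/0.85 = 74.1, rounded up to 75. With 72 enrolled and 15% lost, 72 × 0.85 = 61.2 remain. The 63 itself does not reproduce from the stated inputs (117 per arm for 50 mm, SD 136 mm, two-sided 0.05 and 80% power). That is a separate matter and does not affect this point.

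**Shift in one arm's mean, normal model.** Suppose there is no treatment effect and a fraction q of one arm is lost, namely those highest on a variable that correlates r with outcome. The mean of those who remain falls by

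shift = r × SD × φ(c)/(1 − q), where c is the (1 − q) quantile of the standard normal.

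With q = 0.15: c = 1.036, φ(c) = 0.2332, and 0.2332/0.85 = 0.274.

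- r = 1: 0.274 × 136 = 37.3 mm
- r = 0.5: 18.7 mm
- r = 0.3: 11.2 mm
- r = 0: 0 mm

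**Skewed model.** An amplitude cannot be negative, and a normal with mean 76 and SD 136 puts about Φ(−76/136) = Φ(−0.56) = 29% below zero. A lognormal with the same mean and SD has σ² = ln(1 + (136/76)²) = 1.436, so σ = 1.198. With r on the log scale, the mean of those who remain is 76 × Φ(1.036 − rσ)/0.85.

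- r = 1: shift about 37 mm
- r = 0.5: shift about 16 mm
- r = 0.3: shift 8.9 mm

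For r between 0.3 and 0.5 the range is therefore 11 to 19 mm (normal) or 9 to 16 mm (lognormal). The range of 9 to 19 mm spans both.

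**Simulation.** 36 per arm, normal outcome, SD 136 mm, no true effect, two-sample t-test, 10,000 runs. Loss is rounded to whole patients, so 15% is 5 of 36 and the shifts come out slightly smaller than the formula gives.

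| Loss, Zhan Zhuang vs walking | r | False difference (mm) | Rejection rate at 0.05 |
|---|---|---|---|
| 15% vs 0% | 1 | −34 | 20% |
| 15% vs 0% | 0.5 | −17 | 8% |
| 15% vs 5% | 1 | −18 | 12% |
| 15% vs 5% | 0.5 | −9 | 7% |
| 15% vs 15% | 0.5 | near 0 | 5% |
| 15% vs 0% | 0 | near 0 | 5% |

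With equal loss and r = 1 the mean difference is also near zero, although the rejection rate is 9%.

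**The case against.** The strongest reply is that the document never says these patients' data are discarded. Table 1 schedules the week 9 and week 17 assessments without excepting anyone, no analysis set is defined, and a condensed article may leave that to an analysis plan. This stands. A reader might infer that the trial will compare only patients who adhered and did well; the text permits that but does not state it.

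A reader might also take the 15% allowance to consist of patients removed under these criteria. The Sample size section does not say what the allowance covers. Inflating for ordinary drop-out is routine and compatible with an as-randomised analysis.

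Unequal detection is likewise an inference. It rests on where the calendar sentence sits. The walking group's training is monitored for intensity, and nothing says its attendance goes unrecorded. It remains true that an adherence record is described for one arm only.

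Finally, 37 mm requires loss from one arm only, the full 15% lost for these reasons, and perfect correlation with outcome. None of the three is documented, so it cannot serve as the expected bias.

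What the reply does not remove: poor compliance is listed as a reason for termination or shedding, stopping exercise is not distinguished from leaving the study, and follow-up after withdrawal is described for adverse events only. Followed literally, the criteria can cost outcome data that cannot be recovered later.

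**Conclusion.** The point holds as a defect in the wording of the criteria. They permit loss of outcome data that is related to outcome and possibly unequal between arms, and so a comparison closer to adherers only. They do not establish that this will happen.

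The size rests on assumptions, because no loss rates by arm are given. With 15% lost from one arm only and a correlation of 0.3 to 0.5 with outcome, the false shift is about 9 to 19 mm, or 18% to 38% of the planned 50 mm (9/50 and 19/50). The upper bound is 37 mm. The shift is near zero if loss is equal across arms or unrelated to outcome. Losing deteriorating patients flatters the arm they leave. The direction for non-compliers is not known in advance.

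**What to change.** State in Termination/shedding criteria that meeting a criterion may end the training but does not end study participation, and that non-compliance is not a reason to drop a patient from outcome assessment. Keep the scheduled week 9 and week 17 visits for every patient who still consents, and analyse each in the arm to which they were randomised. Give the same exercise calendar to both arms. Report any adherence-based analysis as secondary. Leave the clinical rule for when training stops unchanged.

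The cost is a few sentences and one printed calendar per walking patient; the visits are already in Table 1. The small downside is that including non-adherers may dilute the estimated effect.

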### Sample size

This study is designed as a randomised controlled trial. The main outcome is the mean relief of upper limb static tremor after treatment. A review of previous studies showed that aerobic exercise could reduce upper limb static tremor amplitude by approximately 60%. It is estimated that the average tremor amplitude of the control group is approximately 76±136 mm, and the intervention group is expected to be reduced by 50 mm after training. The test level α is set at 0.05 (bilateral), the degree of certainty 1-β is set at 0.80 and the control:intervention group ratio=1:1. A sample size of 63 was calculated using *http://powerandsamplesize.com*. However, considering an abscission rate of about 15%, 72 patients with PD will be included.

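### The 50 mm planning difference rests on evidence about aerobic exercise, which the control arm also receives, so neither it nor the 80% power is supported for Zhan Zhuang versus walking

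*Protocol article*

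**What the plan says.** The Sample size section takes tremor relief as the outcome for sizing ("The main outcome is the mean relief of upper limb static tremor after treatment"). It cites prior evidence that "A review of previous studies showed that aerobic exercise could reduce upper limb static tremor amplitude by approximately 60" per cent. It then states that "the average tremor amplitude of the control group is approximately 76±136 mm" and that "the intervention group is expected to be reduced by 50 mm after training". It uses a two-sided 0.05 level, 80% power and 1:1 allocation, arrives at 63, and adds about 15% for dropout to reach 72, or 36 per arm. No change is stated for the control group.

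Study design and setting describes the comparator: "The control group will be treated with conventional medicine and routine aerobics". The exercise is walking, in five 30-minute sessions a week for 8 weeks, at 60%–80% of HRmax or RPE 11–13. The Zhan Zhuang arm also takes conventional medicine. After a learning week it practises five times a week for 30 minutes in the same intensity band. The Introduction and Discussion both class Zhan Zhuang as aerobic exercise.

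The abstract describes only one side: "The intervention group received conventional medicine plus Zhan Zhuang Qigong exercises five times a week at 30 min each time". It does not mention walking. The objective under Methods and analysis reads: "The main objective is to investigate the effects of Zhan Zhuang on upper limb static tremor and aerobic capacity".

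**The concern.** The evidence behind the effect size concerns aerobic exercise as such, and both arms receive aerobic exercise. It can support an expected fall within an exercising arm. It cannot by itself support a difference between two arms that exercise on the same schedule. If walking has any benefit on tremor and the level expected after Zhan Zhuang stays where the plan puts it, the true difference is below 50 mm and power is below whatever 50 mm would give.

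The wording of the claim is also affected. A randomised comparison with walking estimates the effect of Zhan Zhuang relative to walking. A reader of the abstract alone would take it as Zhan Zhuang added to usual care, which is a different and larger claim. The objective names both tremor and aerobic capacity, and the comparator is the same for both.

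**Working it through.** **Inputs.** From Sample size: control mean 76 mm, SD 136 mm, reduction 50 mm, two-sided α = 0.05, power 0.80, 1:1, 72 patients. From Study design and setting: both arms exercise aerobically. Assumed, because the documents do not give it: the share r by which walking reduces tremor.

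**Step 1: the plan's own figure.** Per-arm size for two means is n = 2 × SD² × (1.960 + 0.842)² / δ². With the stated inputs this is 2 × 136² × 7.849 / 50² = 116.1, so 117 per arm, or 234 in total. The stated 63 is not reproduced per arm or in total. (63 per arm follows from δ/SD = 0.5, which needs an SD of about 100 mm instead of 136 mm.) This error is separate from the comparator question, but it sets the starting point.

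**Step 2: power at 36 per arm for the full 50 mm.** Two-sample t-test, 70 degrees of freedom, noncentrality (δ/SD) × √(36/2). Here (50/136) × 4.243 = 1.56, giving power of 34%.

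**Step 3: where 50 mm comes from.** 50/76 = 66%, and 60% of 76 mm is 45.6 mm. The planned reduction is close to the cited effect of aerobic exercise. No other source is offered.

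**Step 4: let walking have some effect.** Hold the Zhan Zhuang level at 76 − 50 = 26 mm. The control level is 76 × (1 − r), so δ = 50 − 76r. Power is for 36 per arm with no dropout, computed in two ways:

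- Constant SD of 136 mm in both arms.
- SD proportional to the mean, at 136/76 = 1.789. The Zhan Zhuang SD is then 1.789 × 26 = 46.5 mm and the control SD is 1.789 × 76(1 − r). The SD used is the root mean square of the two.

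| Walking reduction r | Control level (mm) | δ (mm) | Power, SD 136 | Control SD if scaled (mm) | SD used if scaled (mm) | Power, SD scaled |
|---|---|---|---|---|---|---|
| 0% | 76.0 | 50.0 | 34% | 136.0 | 101.6 | 54% |
| 20% | 60.8 | 34.8 | 19% | 108.8 | 83.7 | 41% |
| 30% | 53.2 | 27.2 | 13% | 95.2 | 74.9 | 33% |
| 40% | 45.6 | 19.6 | 9% | 81.6 | 66.4 | 23% |
| 60% (upper bound) | 30.4 | 4.4 | 5% | 54.4 | 50.6 | 7% |

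**Step 5: separate the two causes.** With constant SD, the drop from 80% to 34% (46 points) comes from the sample size arithmetic. Walking at 20%, 30% and 40% then takes off about a further 15, 20 and 24 points (33.7 − 18.8, 33.7 − 13.3, 33.7 − 9.3). Both the starting point and the further loss depend on the SD assumption, as the last column shows.

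**The case against.** Four objections deserve an answer.

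*The plan never says that controls stay unchanged.* This is correct. A reader might infer that the plan assumes no improvement under walking, but the control mean of 76 mm carries no time point and could be the level expected under the control regimen. That reading does not rescue the 50 mm. It would then be a gain over and above walking, and the only evidence cited is for aerobic exercise itself. On either reading the difference lacks support; only the stronger statement about what the planners assumed has to be dropped.

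*The 60% need not apply to walking.* This is also fair. A reader might conclude that the trial has about 5% power. That requires walking to produce the whole cited reduction, and the document does not claim so. The one result on upper limb tremor amplitude that its Discussion describes is for upper limb centrifugal exercise, and its Introduction says that walking aggravates tremor, apparently as an acute effect. The 60% row is therefore an upper bound.

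*Walking is a legitimate comparator.* It is, and it is openly described with a guideline reference. The objection is to the effect size and the wording, not to the choice.

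*A null result will not necessarily be misreported.* A reader might expect the plan to declare no effect, or equivalence, if p exceeds 0.05. Statistical analysis sets a significance threshold and contains neither rule, so this is not a defect of the document.

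**Conclusion.** The point holds in a limited form. The 50 mm difference is not justified for the contrast being randomised, because its only stated support is an effect of aerobic exercise and both arms exercise aerobically on matched schedules. The 80% power therefore does not describe this trial.

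The size depends on two things that the documents do not give: the effect of walking on tremor, and how the SD behaves as amplitude falls. For assumed walking reductions of 20% to 40%, power with 36 per arm is about 19% to 9% at constant SD, or 41% to 23% with SD proportional to the mean. These figures should be read against starting points of 34% and 54%, not against 80%. They also assume that the Zhan Zhuang arm reaches 26 mm and that nobody drops out. The direction is firm under that first assumption: any benefit of walking lowers power. The exact loss is not known.

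The abstract's silence on walking and the unqualified objective are matters of clarity, but they matter here because the comparator defines what is estimated.

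**What to change.** In Sample size, replace the present justification with an expected difference between Zhan Zhuang and walking, its SD and the reason for both, and restate the power that 36 per arm gives for that difference. If no evidence on walking is available, say so and show power over a range, with the SD assumption stated. Correct the separate arithmetic (63 against 117 per arm on the stated inputs) in the same revision, so that the two causes of low power are not confused.

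In the objective and the abstract, name the contrast as Zhan Zhuang versus walking, both added to conventional medicine, and limit the conclusion to it.

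The cost is a less favourable stated power and a narrower headline claim. This is a change of text only: treatment and patient number do not change, so the revision makes the power honest but does not raise it.

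### The 50 mm target is about 66% of the stated 76 mm, more than the cited 60%, and the stated inputs give neither 63 patients nor 80% power

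*Protocol article*

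**What the plan says.** The Sample size section of the protocol article sets out the calculation in a few sentences. It reports from a review of earlier studies that "aerobic exercise could reduce upper limb static tremor amplitude by approximately 60" per cent. It then estimates that "the average tremor amplitude of the control group is approximately 76±136 mm" and states that "the intervention group is expected to be reduced by 50 mm after training". The test is two-sided at 0.05, "the degree of certainty 1-β is set at 0.80", and allocation is equal. From these inputs, "A sample size of 63 was calculated using" an online calculator. Finally, "considering an abscission rate of about 15%, 72 patients with PD will be included".

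The section on mobile exercise test data says that phone amplitudes will be compared between groups with an independent two-sample t-test, or with non-parametric tests if the data are not normal. Study design and setting says that the control group also exercises: walking, as the chosen aerobic mode, five times a week for 30 minutes over 8 weeks.

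**The concern.** Two things fail to fit. First, the only evidence offered for the expected effect is a reduction of about 60%, and the only mean it can be applied to is 76 mm. Together they give less than 50 mm, so the design rests on a larger effect than the one cited.

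Second, the planned difference is small beside the SD: 50/136 is 0.37 of an SD. A two-arm trial needs well over 63 patients to detect that with 80% power.

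At stake is the power claim. A reader would take the trial to have an 80% chance of detecting the planned effect and might read a null result as evidence against the intervention. On the section's own figures, the chance of missing the planned effect is about two in three.

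**Working it through.** **Inputs**, all from the Sample size section: control mean 76 mm; SD 136 mm; difference 50 mm; cited reduction about 60%; two-sided alpha 0.05; power 0.80; allocation 1:1; 63 before dropout; dropout about 15%; 72 in total, so 36 per arm. I assume that 136 mm is the SD of the analysed amplitude in each arm and that the 50 mm is used as the between-group difference.

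**Percentage against millimetres**
- 0.60 × 76 = 45.6 mm.
- 50/76 = 0.658, so 50 mm is a reduction of about 66%. Even 65% of 76 mm is only 49.4 mm.
- 50/45.6 = 1.096, so the target is 9.6% larger than the cited effect implies.
- At a fixed SD, sample size varies with the inverse square of the difference: (50/45.6)² = 1.20.

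**Trying to reproduce 63**

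Normal approximation: n per arm = 2 × [SD × (1.960 + 0.842)/difference]².
- At 50 mm: 2 × (136 × 2.802/50)² = 116.1, so 117 per arm and 234 in total.
- At 45.6 mm: 2 × (136 × 2.802/45.6)² = 139.6, so 140 per arm and 280 in total.

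The two-sample t-test gives 117.1 and 140.6 per arm, so 118 and 141 after rounding up.

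Other readings of the same inputs at 50 mm:

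| Calculation | n |
|---|---|
| Two-arm, one-sided | 92 per arm |
| One-sample or paired, normal | 59 |
| One-sample or paired, t | 61 |

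No two-arm version gives 63, in total or per arm. The paired t figure of 61 is nearest, but it is not the design described. For 63 in total to give 80% power at 50 mm, the SD would have to be about 71 mm (50 × √(31.5/2)/2.802 = 70.8).

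The step to 72 is a smaller matter: 63 × 1.15 = 72.45, whereas allowing for 15% loss means 63/0.85 = 74.1, so 75.

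**Power that 72 patients deliver** (two-sample t-test, SD 136 mm)

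| Analysed per arm | 50 mm | 45.6 mm |
|---|---|---|
| 36 (no dropout) | 34% | 29% |
| 30.6 (36 × 0.85) | 29% | 25% |

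The normal approximation gives 34% and 30% in the first row, so the choice of formula hardly matters.

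**The case against.** The strongest reply concerns the first mismatch. The section never says that 50 mm was calculated as 60% of 76 mm. It marks both the percentage and the mean as approximate, and planning differences are often round numbers. Nor does it say whether 76 mm is a baseline value. If it is the control mean after eight weeks of walking, the baseline could be higher; as an illustration only, a baseline of 83.3 mm would make 50 mm exactly 60%. All of this stands. A reader might infer a proven conversion error, but the text does not support that. What remains is that the figures as printed do not agree, that the gap is in the favourable direction, and that no baseline near 83 mm or other source is given.

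A reader might also infer from the ratio of 1.20 that this trial is about 17% too small (1 − 1/1.20). That figure compares a size correctly computed at 50 mm with one at 45.6 mm. It does not describe this trial, whose 63 does not come from 50 mm and SD 136 mm in any two-arm calculation tried.

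On the second mismatch, one could say that 136 mm overstates the SD relevant to the analysis, for instance if changes from baseline are compared and vary less. That is possible, but the section gives no other SD, and one near 71 mm would be needed. An SD well above the mean of an amplitude also suggests a skewed distribution, so the rank test may be the one used and t-test power is then only a guide. That is no support for the stated 80%.

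**Conclusion.** The point holds in two parts of unequal weight. The lesser is that 50 mm is about 66% of the stated mean, against a cited 60% or 45.6 mm, without explanation. On its own this moves power at 36 per arm only from 34% to 29%.

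The greater is that the stated inputs require about 118 per arm (141 at 45.6 mm), not 63 in total, and that 72 patients give roughly 25% to 34% power instead of 80%, depending on the difference and the dropout. These figures rest on SD 136 mm applying to the analysed amplitude in each arm and on a two-sample comparison.

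The 60% is, if anything, generous as a between-group difference: it is an effect of aerobic exercise, and the control arm also does aerobic walking. The documents give no figure for how much tremor falls with walking, so this cannot be sized.

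**What to change.** In the Sample size section:

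1. Make the percentage, the mean and the millimetre difference agree. Either use 45.6 mm (60% of 76 mm), or keep 50 mm, describe it as about 66% and give its basis. Say whether 76 mm is a baseline or a post-treatment value.
2. Withdraw the statement that these inputs give 63 patients at 80% power. State instead the power for the planned 72: about 34% at 50 mm or 29% at 45.6 mm with all analysed, and about 29% or 25% after 15% dropout. If another SD or formula lay behind the 63, report it and show the calculation.
3. Add a sentence saying that the 60% is an aerobic-exercise effect, that the comparator is also aerobic exercise, and why the full effect is or is not expected as a difference between arms.

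The cost is a few sentences and one recalculation. No extra enrolment is required. The downside is that the stated power becomes much less favourable, and a null result would have to be read as inconclusive.
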